**PROTOCOL**

**Background & Rationale**

Atherosclerosis is a progressive, yet initially asymptomatic disease in which the accumulation of lipids, inflammatory cells and other connective tissue cells result in endothelial dysfunction, arterial stiffness and eventual narrowing or even occlusion of affected arteries after rupture of an inflamed, unstable atheromatous plaque. The incidence of cardiovascular disease varies throughout Europe with a reduced incidence in those areas with a Mediterranean diet which contains a larger proportion of fruit, vegetables and olive oil and has been well published over the last 20 years^1-3^.

Dietary therapies such as the Mediterranean diet have been shown to be associated with a reduced risk of atherosclerotic diseases ^4^ in particular the intake of tomatoes and tomato-based products. The reasons postulated are that such diets are rich in antioxidants. Lycopene is a lipophilic, active carotenoid component of tomatoes – and levels of lycopene in plasma or adipose tissue are inversely correlated to risk of disease. It is one of the most potent antioxidants with a singlet-oxygen quenching ability twice that of β-carotene and 10 times that of α-tocopherol^5^. The bioavailability of lycopene varies according to the preparation of tomatoes – for example it is very bioavailable in the presence of oil. Tomato paste also has enhanced bioavailability compared to raw tomatoes, tomato juice or to tablets/capsules containing highly concentrated tomato extract. Additionally, tomatoes of different origins, sizes, shapes, and the nature in which it is consumed has profound effects on the amount of lycopene it contains. This explains why there is a variable correlation between tomato intake and plasma/adipose lycopene levels and disease risk.

There have been no studies of standardised intake of tomato extract to examine its effect on vascular physiology to date. There are association studies that inversely link lycopene levels with surrogate endpoints of cardiovascular disease or its incidence both in adipose tissue and serum. ^6, 7^

Endothelial function as measured by forearm blood flow (plethysmography) is a well described method of assessing and determining vascular function and can interrogate endothelium dependent and independent mechanisms of nitric oxide bioavailability^8^ and can predict risk of future events^9^. Arterial stiffness is now rapidly being accepted as a measure of functional and structural changes which accompanies cardiovascular disease and is increasingly associated with outcomes^10^.

We would like to determine whether a standardised preparation of tomato extract containing a defined amount of lycopene may have effects on vascular physiology. We wish to investigate the effects of a standardised tomato extract product (using a commercially available nutritional supplement - Ateronon) produced by a high quality food manufacturer on vascular function (endothelial function and arterial stiffness).

We plan to study this in 2 groups of subjects – healthy older people and stable cardiovascular disease patients on stable statin therapy.

**Hypotheses**

1. Dietary supplementation with a standardised tomato extract product improves endothelial function in healthy older people and patients with stable cardiovascular disease.
2. Dietary supplementation with a standardised tomato extract product improves parameters of arterial stiffness.
3. Dietary supplementation with a standardised tomato extract product reduces lipoprotein oxidation and circulating markers of endothelial damage.

**Study Objectives**

Dietary supplementation with a standardised tomato extract product improves endothelial function in healthy older people and patients with stable cardiovascular disease.

**Study Design**

Subjects will be screened, then randomised to receive Ateronon or placebo for 56 days. Randomisation will be unequal for each group (ratio 2:1 drug:placebo). Forearm plethysmography studies will be conducted pre-dose and at the end of the treatment period. Arterial stiffness will also be measured at both study visits.

**Visit 1** **Screening Visit 2 Treatment Visit 3 Follow-up**

**(4 weeks) Randomisation (8 weeks) End of (2 weeks)**

**Treatment**

**Key Assessments (Visits 2 & 3)**

arterial stiffness, forearm blood flow, blood sampling for lipoprotein oxidation and markers of endothelial damage

**‘Healthy’**

- 30-80 years
- Non-smoking
- No hypertension/CVD
- No renal/respiratory/

neurological disease

- No diabetes

24 tomato extract o.d.

12 placebo o.d.

**‘Stable CVD’**

- 40-80 years
- Previous IHD (MI, stent, angina), TIA or ischaemic stroke disease or peripheral vascular disease
- Statin use stable

24 tomato extract o.d.

12 placebo o.d.

**Figure 1.** Study Design

**Number of Participants**

a) Sufficient numbers will be recruited to complete 36 healthy older male or female subjects (‘Healthy Group’)

AND

b) Sufficient numbers will be recruited to complete 36 stable cardiovascular disease patients on stable statin therapy (‘Stable CVD Group’).

Subjects will be asked to continue their intake of tomato and tomato based products as before (*i.e.* not to change their intake whilst on the study) to reduce interference with the study question. Other potential confounding effects of vascular function *e.g.* glucose, lipid profile and blood pressure will also be measured.

**Outcome Measures**

**Primary outcome:**

Forearm blood flow ratio and/or absolute flow in the infused arm (& % change), as measured by venous occlusion plethysmography, in response to intra-arterial acetylcholine infusion.

**Secondary outcomes:**

- Forearm blood flow ratio and/or absolute flow in the infused arm (& % change), as measured by venous occlusion plethysmography, in response to intra-arterial sodium nitroprusside infusion.
- Forearm blood flow ratio and/or absolute flow in the infused arm (& % change), as measured by venous occlusion plethysmography, in response to intra-arterial L-NMMA infusion.
- Augmentation index (an indicator of arterial stiffness) as estimated by radial arterial pulse contours.
- Pulse wave velocity measured between carotid and femoral artery.
- Lipoprotein oxidation/circulating markers: LDL oxidating activity, AtheroAbzymes, CRP, lipoprotein profile, adiponectin, TNF, IL-2, IL-6, endothelial progenitor and endothelial shedded cells, lycopene concentration in serum, urinary isoprostanes
- Safety and tolerability parameters, including physical examination, blood pressure, heart rate, 12-lead electrocardiograms (ECGs), clinical laboratory tests and adverse event reporting.

**Participants**

**Inclusion criteria (Healthy Group)**

- Aged between 30 and 80 years
- Non-smoking (never smoked regularly [ie >5 cigarettes per day] within past 5 years.)

**Exclusion criteria (Healthy Group)**

- Hypertension (Sustained BP>160/100mmHg), or other cardiovascular disease
- Use of a statin within the preceding three months, or at study start
- Significant renal, respiratory or neurological disease
- Diabetes mellitus
- BMI>32 kg/m^2^, BMI<18 kg/m^2^
- Pregnant or taking the combined oral contraceptive pill or hormone replacement therapy
- Use of vasoactive or other medication including regular NSAIDs
- Use of heparin or warfarin
- Allergy to tomato or tomato products
- Lactose intolerance
- Allergy to whey protein or soy protein
- Any concomitant condition that, at the discretion of the investigator, may affect the participant’s ability to complete the study
- Lack of informed consent
- Current involvement in other research studies

**Inclusion criteria (Stable CVD Group)**

- Aged between 40 and 80 years
- Previous ischaemic heart disease (any of previous myocardial infarction, coronary stent, angina diagnosed on angiography/other imaging modality or exercise/stress testing), transient ischaemic attack or stroke disease or peripheral vascular disease
- If taking a statin, dose must have been stable over preceding 2 months.

**Exclusion criteria (Stable CVD Group)**

- Uncontrolled hypertension BP>180/110
- BMI > 35kg/m^2^
- Pregnant or taking the combined oral contraceptive pill or hormone replacement therapy
- Use of heparin or warfarin
- Allergy to tomato or tomato products
- Lactose intolerance
- Allergy to whey protein or soy protein
- History of active malignant cancer (excluding non-melanoma skin cancer) in the past 3 years.
- Any concomitant condition that, at the discretion of the investigator, may affect the participant’s ability to complete the study.
- Lack of informed consent
- Current involvement in other research studies

**Withdrawal Criteria**

Participants will be withdrawn if unable to tolerate study substance.

**Study Visits**

**Screening – Visit 1 (Days -28 to -1)**

Informed consent, medical history, physical examination, height and weight, 12 lead ECG, BP and other vitals, pregnancy testing (urine) for women of child-bearing potential, concomitant medications. Home blood pressure measurements to be taken morning and evening on 7 days between Visit 1 and Visit 2.

**Visit 2 (Day 0)**

Randomisation. BP and vitals, concomitant medications, weight, arterial stiffness measurements, 12 lead ECG, blood sampling, urine sampling, then forearm study. First dose to be taken that evening.

**Days 1 to 55**:

Daily dosing with Ateronon or placebo. Home blood pressure readings to be taken morning and evening on 7 of the 14 days preceding Visit 3.

**Visit 3 (Day 56 +/- 7 days)**

BP and vitals, concomitant medications, weight, arterial stiffness measurements, 12 lead ECG, blood sampling, urine sampling, then forearm study.

**Follow-up (Day 70 +/- 7 days)**

Telephone screen 2 weeks after Visit 3.

# Participant restrictions

# Participants will be required to refrain from caffeine, alcohol and strenuous exercise for 24 hours prior to Visits 2 and 3, and to fast for a minimum of 4 hours prior to these visits. Participants must not take aspirin, vasoactive/blood pressure medication on the day of Visit 2 or 3 until after the visit.

# Methods

# Blood pressure measurement

Blood pressure will be measured in the seated position after 5 minutes rest. A validated machine will be used. Validated home monitors will be issued to subjects for recording home blood pressure. 3 readings will be made and the average of the last 2 will be used for the average. For home blood pressure measurements, participants will record the 2^nd^ and 3^rd^ readings in the participant diary.

**12-lead ECG**

A 12-lead ECG will be recorded with the participant resting supine.

**Blood Sampling**

***Visits 2 & 3***: 50ml of venous blood will be drawn for estimation of plasma lycopene, standard haematology/chemistry (to include urea and electrolytes, hsCRP, full cholesterol profile), endothelial progenitor cells, oxidised LDL, and other biomarkers of inflammation (eg LDL oxidating activity, AtheroAbzymes, CRP, lipoprotein profile, adiponectin, TNF, IL-2, IL-6, endothelial progenitor and endothelial shedded cells).

**Urine Sampling**

A sample of urine will be collected for measurement of isoprostanes.

Arterial stiffness measurements

Measurements will be made using a non-invasive tonometer applied to the carotid, radial and femoral arteries in the seated and supine position for measurement of pulse wave analysis and aortic pulse wave velocity.

# Forearm blood flow studies

Forearm blood flow will be measured simultaneously in both arms using venous occlusion plethysmography with mercury-in-silastic strain gauges electrically calibrated. The laboratory will be quiet and the temperature will be controlled at 23 ± 2OC. A 27 gauge un-mounted steel needle will be inserted into the non-dominant brachial artery under local anaesthesia (1% lignocaine hydrochloride). Saline or drugs will be infused at a constant rate of 1.0 ml/min by means of a constant rate infusion pump. Basal blood flow will be recorded after 30 min of saline infusion. Acetylcholine (7.5 & 15 µg/min) will then be infused intra-arterially at 1 ml/min as a measure of endothelial NO activity. Each dose will be infused for 6 minutes and forearm blood flow will be measured for 3 minutes at the end of each infusion period. The means of these measurements will be used for analysis. After a further 30 min washout with

**SNP**

3 µg /min

**Saline** 0.9%

**Saline** 0.9%

**ACh** 7.5 µg/

min

**L-NMMA**

4 µmol/

min

0 (minutes) 30 36 42 72 78 84 114 120 126 136

needle 15-18 21-24 27-30 33-36 39-42 63-66 69-72 75-78 81-84 105-108 111-114 117-120 123-126 insertion FBF FBF FBF FBF FBF FBF FBF FBF FBF FBF FBF FBF FBF

**BL1 BL2** **BL3 A1 A2 BL4 BL5 S1 S2 BL6 BL7 L1 L2**

**ACh** 15 µg/

min

**SNP** 10 µg /min

**L-NMMA** 2 µmol/

min

**Saline** 0.9%

**Saline** 0.9%

BP/HR BP/HR BP/HR BP/HR BP/HR BP/HR BP/HR

**Figure 2**. Schematic for measurement of forearm blood flow (FBF). Saline is infused to establish a baseline (BL) before infusion of each challenge agent. BL3, BL5 and BL7 are used as the challenge agent-specific baselines for acetylcholine (ACh), sodium nitroprusside (SNP) and N^G^-monomethyl arginine (L-NMMA), respectively. Each dose of challenge agent is infused for 6 minutes, and FBF recorded in both arms over the last 3 minutes of each infusion.

**Saline** 0.9%

saline, the NO donor, sodium nitroprusside (SNP) will be infused intrarterially at 2 doses (3 and 10 µg/min) for 6 minutes each to test for NO-independent mechanisms. Finally, the NO antagonist L-NMMA will be infused after a 30 minute saline washout, again at 2 doses (2 and 4 µmol/min) and FBF measured as before. A final 30 minutes of saline will then be infused. Blood pressure and heart rate will be recorded at baseline, and at the end of each infusion. The total duration of the assessment is 2 hours and 16 minutes.

**Food Supplement Details**

Ateronon™ is a naturally sourced food supplement consisting of the following ingredients:

Tomato extract (lycopene), whey protein (from milk,) soy, microcrystalline cellulose, gelatine, calcium phosphate, silicon dioxide, polysorbate, glyceryl behenate, colours (red iron oxide, titanium dioxide). All ingredients have been certified as food.

**Supplies**

Ateronon and matching placebo capsules (red in colour) will be provided by Cambridge Theranostics Ltd. Upon randomisation, participants will receive sufficient capsules for the whole treatment period.

**Dosing**

One capsule will be taken daily, in the evening with or immediately after food, throughout the 56-day treatment period.

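### The fixed 56-day course and a Visit 3 window of Day 49 to Day 63 do not fit together: read literally, the primary forearm study can fall 8 calendar days after the last scheduled capsule

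*Protocol*

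**What the plan says.** Five parts of the protocol bear on this.

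- **Study Design** fixes the length of treatment: "Subjects will be screened, then randomised to receive Ateronon or placebo for 56 days". It also fixes when the forearm studies take place: "Forearm plethysmography studies will be conducted pre-dose and at the end of the treatment period".
- **Study Visits, Visit 2 (Day 0)** gives the start: "First dose to be taken that evening". The next entry, headed Days 1 to 55, reads "Daily dosing with Ateronon or placebo".
- **Study Visits, Visit 3** sets the window for the second forearm study: "Visit 3 (Day 56 +/- 7 days". The study diagram and Appendix 1 label this visit End of Treatment.
- **Dosing** repeats the fixed length: "One capsule will be taken daily, in the evening with or immediately after food, throughout the 56-day treatment period".
- **Supplies** says that, at randomisation, "participants will receive sufficient capsules for the whole treatment period". It gives no capsule count.

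The primary outcome is forearm blood flow "as measured by venous occlusion plethysmography, in response to intra-arterial acetylcholine infusion", so the Visit 3 forearm study supplies its post-treatment value.

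**The concern.** Treatment has a fixed length, while the visit meant to measure its effect may move a week either way. If the dosing days are taken as written, a late Visit 3 measures participants who have stopped the supplement. That does not match the stated aim of measuring at the end of the treatment period. An early Visit 3 measures participants who have had a shorter course.

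The trial's hypothesis concerns supplementation, so a measurement made after it stops tends to understate an effect that fades. Unequal exposure across participants adds variability. Dosing days, supply and visit windows are protocol matters, and an analysis plan cannot restore exposure on the day of measurement.

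**Working it through.** **Inputs, all from the protocol.** First capsule on the evening of Day 0 (Visit 2). Daily dosing on Days 1 to 55 (Study Visits). Treatment period of 56 days (Study Design; Dosing). Visit 3 on Day 56 plus or minus 7 days (Study Visits).

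**Step 1: reproduce the stated length.** One capsule on Day 0 plus 55 capsules on Days 1 to 55 gives 1 + 55 = 56. This matches the 56-day period exactly, with the last scheduled capsule on the evening of Day 55.

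**Step 2: the Visit 3 window.** 56 − 7 = Day 49 and 56 + 7 = Day 63, so 63 − 49 + 1 = 15 permitted days. Of these, Days 57 to 63 (7 days) come after the nominal Day 56 visit.

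**Step 3: exposure at the visit, on the literal reading.** The clock times are an assumption: capsule at 19:00 and visit at 09:00, so the gap is 24 hours per calendar day minus 10 hours.

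| Visit 3 on | Doses taken | Last capsule before the visit | Calendar days since | Approximate time since |
| --- | --- | --- | --- | --- |
| Day 49 | 49 (Days 0 to 48) | Day 48 | 1 | 24 − 10 = 14 h |
| Day 56 | 56 (Days 0 to 55) | Day 55 | 1 | 24 − 10 = 14 h |
| Day 63 | 56 (Days 0 to 55) | Day 55 | 8 | 8 × 24 − 10 = 182 h, about 7.6 days |

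The nominal Day 56 visit is therefore consistent with daily evening dosing. The early side changes the number of doses, and the late side changes the time since the last dose. If the last capsule were taken on Day 56 instead, the longest gap would be 63 − 56 = 7 calendar days.

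**Step 4: look for text that closes the gap.** No section says that dosing continues until a late Visit 3, that spare capsules are issued for one, or that the visit must fall within a set time of the last capsule.

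**Step 5: can the dilution be sized?** No. It would need how fast any vascular effect fades, how visits spread over the window, and whether late participants actually stop at Day 55. The protocol gives none of these. The following is illustration only. Assume that all late participants stop on schedule, that the effect is full up to Day 56, and that it then fades with half-life h, so the share left k days later is 2^(−k/h).

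- Visits spread evenly over the 15 days: mean share retained = (8 + Σ 2^(−k/h), k = 1 to 7) / 15, which is 0.74 for h = 3 days and 0.89 for h = 10 days.
- Visits clustered on Day 56 with weights 8 − |k|, which sum to 64: mean share retained = (36 + Σ (8 − k) 2^(−k/h), k = 1 to 7) / 64, which is about 0.80 for h = 3 and 0.92 for h = 10.
- Dosing continued to the visit: 1, no loss from stopping.

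The spread of these answers reflects the assumptions, not the trial.

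**The case against.** The strongest reply is that the day numbers are nominal and that treatment ends at the actual Visit 3. Three things support it.

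- The visit is labelled End of Treatment, and the study diagram gives the treatment period as 8 weeks.
- Follow-up is set both at 2 weeks after Visit 3 and at Day 70 plus or minus 7 days. Since 49 + 14 = 63 and 63 + 14 = 77, that window moves exactly with Visit 3.
- The entry headed Days 1 to 55 places home blood pressure readings on 7 of the 14 days before Visit 3. For a Day 63 visit those are Days 49 to 62, which run past Day 55. The heading may therefore simply mean the interval between visits.

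This makes the reading plausible but does not settle it. The label does not extend a period that is given twice as 56 days. The follow-up timing says nothing about dosing. The home readings can still be completed as headed, because Days 49 to 55 supply exactly the 7 days needed.

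Two parts of the objection stand in full. Stopping on Day 55 is one reading, not the only one. And the Supplies wording cannot be used to show that capsules run out: it gives no count and is compatible with extra capsules for a late visit.

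**Conclusion.** The inconsistency is real and rests only on the protocol's own day counts. A participant can follow every stated rule and have the primary forearm study 8 calendar days after the last scheduled capsule, or after 49 doses instead of 56. The text leaves it open whether dosing continues to a late visit.

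A reader might go further in three ways that the protocol does not support.

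- **That late participants are certainly measured off supplement.** This holds only on the literal reading. If dosing in practice continues to the visit, the off-supplement gap disappears, although the length of the course still varies.
- **That a definite amount of power is lost.** Any such figure needs an assumed fading rate, an assumed spread of visits and universal stopping at Day 55. The illustration above is not an estimate.
- **That the comparison is biased in favour of one arm.** The same window applies to both arms. The risk is attenuation and added variability.

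This is a correctable inconsistency that bears on the primary outcome, and its size is unknown.

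**What to change.** Reconcile Study Design, the Visit 2, Days 1 to 55 and Visit 3 entries, Supplies and Dosing, so that the Visit 3 forearm study always falls within the dosing period. The sponsor decides whether the dosing and supply wording or the visit window changes; this review takes no position on which. If treatment is already meant to run to the actual Visit 3, saying so in those sections removes the off-supplement question.

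As an optional aid, record the date of the last capsule at Visit 3, so that days since the last capsule can be described by arm. The case report form is not shown, so the absence of this field from the protocol is not an error.

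The cost is a few sentences and, depending on the sponsor's choice, a few more capsules per participant or a tighter visit window. The optional record is one date field.

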**Study End**

The study will complete when the last participant in either group completes the follow-up telephone screen, or is withdrawn or lost to follow-up.

**Plan of Further Treatment**

Ateronon^TM^, the standardised tomato extract product being investigated in this study, is commercially available. Participants will be informed of this, enabling them to continue taking the supplement after the study if desired, at their own cost.

# Adverse Events

##

**Definitions**

**Adverse Event (AE):** any untoward medical occurrence in a patient or clinical study subject.

**Serious Adverse Event** **(SAE):** any untoward and unexpected medical occurrence or effect that:

- **Results in death**
- **Is life-threatening** – *refers to an event in which the subject was at risk of death at the time of the event; it does not refer to an event which hypothetically might have caused death if it were more severe*
- **Requires hospitalisation, or prolongation of existing inpatients’ hospitalisation**
- **Results in persistent or significant disability or incapacity**
- **Is a congenital anomaly or birth defect**

Medical judgement will be exercised in deciding whether an AE is serious in other situations. Important AEs that are not immediately life-threatening or do not result in death or hospitalisation but may jeopardise the subject or may require intervention to prevent one of the other outcomes listed in the definition above, should also be considered serious.

Hospitalisations for elective treatment of a pre-existing condition do not need reporting as SAEs.

##

